### Sample size calculation

The study aims to include approximately 2300 patients undergoing SE for the assessment of inducible myocardial ischaemia. The sample size was determined based on anticipated event rates, longitudinal outcome modelling requirements, and the complexity of the proposed ML framework.

Previous SE studies and cardiovascular outcome registries suggest that MACE are expected to occur at sufficient frequency within long-term follow-up to support robust prognostic modelling.^12^ The projected cohort size is anticipated to provide an adequate number of outcome events to satisfy event-per-variable requirements for both conventional statistical analyses and ML-based predictive modelling, while reducing the risk of model overfitting. The proposed sample size is also considered sufficient to support internal cross-validation, subgroup analyses, calibration assessment, and the evaluation of multiple supervised ML approaches, including ensemble methods, support vector machines (SVMs), and neural networks. In addition, linkage with longitudinal NHS outcome datasets over extended follow-up periods is expected to strengthen survival modelling and time-to-event prediction analyses.

External validation using independent multicentre SE cohorts is planned to further assess model generalisability and robustness across different clinical settings.

*
Table 1
* shows the characteristics of the patient population.

**Table 1 qyag143-T1:** Population characteristics

Variable	Total	Positive SE	Negative SE	*P*-value
Anthropometric variables				
*N*	2263	371 (16%)	1892 (84%)	—
Age (years)	63 (55–72)	64 (57–72)	63 (54–72)	0.031
Male Sex	1201 (53%)	243 (65%)	958 (51%)	<0.0001
Race				
Caucasian	2048 (91%)	330 (89%)	1718 (91%)	0.42
Asian	152 (7%)	27 (7%)	125 (7%)	0.85
Black	39 (2%)	8 (2%)	31 (2%)	0.71
Other	24 (1%)	6 (2%)	18 (1%)	0.31
Height (cm)	167 (160–175)	168 (160–176)	167 (160–175)	0.285
Weight (kg)	80 (68–95)	82 (70–98)	79 (67–94)	0.009
BMI (kg/m^2^)	28.7 (24.8–33.5)	29.0 (25.1–33.9)	28.6 (24.7–33.4)	0.198
BSA (m^2^)	1.90 (1.75–2.08)	1.93 (1.78–2.11)	1.89 (1.74–2.07)	0.012
Cardiovascular risk factors factors				
Hypertension	1371 (61%)	240 (65%)	1131 (60%)	0.072
Dyslipidaemia	1345 (59%)	238 (64%)	1107 (59%)	0.031
Current Smoker	218 (10%)	44 (12%)	174 (9%)	0.092
Former Smoker	648 (29%)	114 (31%)	534 (28%)	0.285
Diabetes Mellitus	671 (30%)	127 (34%)	544 (29%)	0.036
Obesity (BMI ≥30)	232 (10%)	30 (8%)	202 (11%)	0.142
Family History of CAD	996 (44%)	154 (42%)	842 (44%)	NS
Medications				
Beta-blockers	1122 (50%)	216 (58%)	906 (48%)	0.0003
ACE-I/ARB	1205 (53%)	233 (63%)	972 (51%)	<0.0001
Anti-platelets	1346 (59%)	260 (70%)	1086 (57%)	<0.0001
Statins	1320 (58%)	235 (63%)	1085 (57%)	0.028
DSE parameters				
Left Ventricular Ejection				
Fraction (rest)				0.005
Preserved (≥50%)	2153 (95%)	340 (92%)	1813 (96%)	
Mild/Moderate (36–49%)	83 (4%)	24 (7%)	59 (3%)	
Severe (≤35%)	24 (1%)	4 (1%)	20 (1%)	
HR at rest (bpm)	68 (60–77)	65 (58–74)	68 (60–78)	<0.001
HR at peak (bpm)	135 (120–147)	131 (115–144)	136 (122–148)	0.018
SBP rest (mmHg)	138 (125–153)	140 (127–156)	137 (124–152)	0.019
SBP peak (mmHg)	140 (118–160)	135 (112–155)	141 (120–162)	0.0110
DBP rest (mmHg)	80 (70–88)	81 (72–90)	79 (70–87)	0.042
DBP peak (mmHg)	70 (60–80)	68 (58–78)	71 (61–81)	0.011
THR achieved	1650 (73%)	260 (70%)	1390 (73%)	0.21
THR at peak (% of MTHR)	100 (90–110)	98 (85–108)	101 (91–111)	0.045
Double product (mmHg*bpm)	18 564 (15 820–21 330)	17 421 (14 650–20 268)	18 765 (16 093–21 560)	<0.001
Biphasic response (viable-ischaemic)	294 (13%)	59 (16%)	235 (12%)	0.072
WMSI at rest	1.05 (1.00–1.18)	1.12 (1.00–1.35)	1.00 (1.00–1.12)	<0.0001
WMSI at peak	1.06 (1.00–1.24)	1.18 (1.05–1.41)	1.00 (1.00–1.18)	<0.0001
Delta WMSI	0.00 (0.00–0.12)	0.05 (0.00–0.18)	0.00 (0.00–0.05)	<0.0001
Positive DSE (inducible ischaemia)	371 (16%)	371 (100%)	0 (0%)	—
Number of inducible ischaemic segments				
0	1896 (84%)	0 (0%)	1896 (100%)	—
1–2	250 (11%)	250 (67%)	0	—
3–4	100 (4%)	100 (27%)	0	—
≥5	21 (1%)	21 (6%)	0	—
QRISK3 score	8.4 (3.4–15.2)	9.6 (4.6–18.2)	8.1 (3.2–14.4)	0.008

Data are: Median (25–75 percentiles) for continuous variables, or *n* (%) for categorical variables. Left ventricular ejection fraction percentages are based on patients with categorized data (*n* = 2260; 21 missing/uncategorizable). Race approximated from ethnicity categories. Comparison by Mann–Whitney test for continuous variables and Chi-square test for categorical variables (for multi-category, overall test). *P* < 0.05 indicates statistical significance.

### Machine learning framework

The proposed ML framework comprises three sequential stages, as illustrated in *Figure 1*. Stage 1 focuses on data preprocessing and baseline risk estimation using the QRISK3 clinical risk calculator. Stage 2 applies supervised ML models to predict disease outcomes and stratify patient risk. Stage 3 integrates longitudinal NHS Digital data with the local Hospital cohort to forecast future cardiovascular events.

### Stage 1: clinical risk modelling and baseline assessment

#### QRISK3 risk estimation

QRISK3 is a validated clinical risk prediction model designed to estimate the 10-year risk of cardiovascular disease (CVD) using demographic and clinical variables.^11^ In this study, QRISK3 is used as a benchmark model against which ML-based approaches are evaluated.

Relevant patient characteristics and CAD risk factors were extracted from the local Hospital dataset and processed using the QRISK3 framework. The resulting risk estimates provide a clinically interpretable baseline for comparison with ML predictions (details of data extraction is provided in the Supplement).

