### Eligibility criteria

#### Inclusion criteria

The study includes consecutive patients, 18 years or older, referred for a SE for inducible ischaemia detection for suspected CAD.

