#### Exclusion criteria

Poor-quality echocardiographic description that preclude accurate interpretation or regional wall motion abnormalities (RWMAs) (thickening) at any stage of the SE protocol. Patients with known allergy to dobutamine or ultrasonic contrast enhancing agents (UCEAs) or who were referred for structural SE to assess severity of valvular abnormalities or left ventricular viability only were excluded. Patients who opted out data sharing were excluded from the study.

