### Data collection

Data were collected using both SE reports and institutional EHR databases. Collected patient demographic information will include age, sex, race, height, weight, and body mass index. Cardiovascular risk factors such as; smoking habits, obesity status, family history of CAD, diabetes mellitus, essential hypertension, dyslipidaemia, prior CAD. Patients’ medical history at the time of the SE was also captured. Patients’ variables in support of calculating the QRISK-3 score^11^ was retrieved as complete as data permitted. (QRISK3 data extraction has been described in Supplement document). Extracted echocardiographic parameters include resting LV ejection fraction (from the WMS), and RWMA Wall Motion Score Index (WMSI) of the left ventricular 17 segments at each or the 4 stages of the SE protocol. (Detailed Dobutamine SE protocol and analysis is described in the Supplementary document.) To address inducible ischaemia the difference of the WMSI between low dose and peak stress of Dobutamine SE was calculated.^4,5^ Vital signs including systolic blood pressure (SBP), diastolic blood pressure (DBP), heart rate (HR) at rest and each stage of the SE protocol (low dose, peak stress, and recovery) were collected.

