### Stage 2: machine learning model development

The cohort is divided into training and validation sets, with 20% of the data held out for internal validation. Supervised machine learning models are developed using demographic characteristics, clinical risk factors, physiological measurements obtained during SE, and imaging-derived variables. The evaluated algorithms include ensemble methods (Random Forest and Gradient Boosting), SVM, and artificial neural networks (ANNs). Hyperparameter optimizations are performed using Bayesian optimization within nested cross-validation. Model selection is based on discrimination, calibration, robustness across validation folds, and clinical interpretability. SHapley Additive exPlanations (SHAP) is subsequently used to quantify feature importance and improve model transparency.

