**Figure 2 qyag143-F2:**
[figure not shown]
FINESSE—machine learning model development workflow.

Baseline risk for each patient will be defined using conventional clinical assessment and QRISK3 derived estimates, as previously described. FINESSE AI will then generate an updated, individualized probability of the outcome of interest at a specified time horizon by integrating echocardiographic parameters, haemodynamic response variables, clinical characteristics, and longitudinal data. The integrated risk estimate will be defined as:

$$R_{F}(i,t)=f(R_{0}(i,t),X_{e}(i),X_{h}(i),X_{c}(i),X_{l}(i))$$

where $R_{0}(i,t)$ represents the baseline risk estimate and the additional inputs correspond to echocardiographic, haemodynamic, clinical, and longitudinal variables, respectively.

To facilitate clinical interpretation, continuous risk estimates will be mapped to predefined categories using a threshold-based classification function. These thresholds will be prespecified and subsequently evaluated against observed event rates within the study cohort to ensure appropriate calibration defined as low risk–intermediate risk–high risk.

Risk reclassification will be defined as a change in category between baseline and FINESSE-derived estimates, expressed as the difference between the categorical assignments derived from $R_{F}(i,\;t)$ and $R_{0}(i,\;t)$. Reclassification will therefore reflect either upward or downward movement across predefined risk strata. To minimize clinically insignificant shifts, reclassification will only be considered when the absolute change in predicted risk exceeds a predefined threshold, anticipated to be in the range of 3–5 percentage points. The predefined 3–5% risk reclassification threshold was selected because it represents the range within which relatively small improvements in estimated cardiovascular risk may influence guideline-directed management decisions, including initiation or intensification of lipid-lowering therapy, additional diagnostic testing, or referral for invasive coronary angiography. Similar thresholds have been adopted in previous cardiovascular risk prediction studies evaluating improvements in discrimination and clinical utility through net reclassification analyses. The threshold was therefore chosen to maximize clinical relevance rather than statistical optimization alone.

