### Patients characteristics & discussion

Quantitative machine learning performance analyses, including comparative AUC, NRI, integrated discrimination improvement, and calibration slope, will be reported in the primary results manuscript and have therefore been intentionally omitted from this protocol paper.

From the 2281 patients 14 patients’ data were excluded from analysis due to their indication for severity of aortic valve stenosis and viability only assessment in 8 and 6 patients respectively. As summarized in *Table 1*, of the 2267 patients undergoing dobutamine SE the median age was 63 years, 53% male, predominantly Caucasian race. Sixty-one percent had the diagnosis of hypertension, 59% dyslipidaemia, 30% diabetes mellitus, 10% current and 29% former smokers, and 10% obese (BMI≥30). The echocardiographic variables indicated 95% of the patients had preserved LVEF. During dobutamine SE 73% of patients achieved target HR (defined as 85% of the age predicted maximum HR), 16% had inducible myocardial wall motion abnormality, and 13% had biphasic response in keeping with viable and ischaemic response. Based on the number of inducible ischaemia of the 17 LV segments low-risk results (no inducible ischaemia) were present in 84%, intermediate-risk results (1–2 new RWMA) in 11%, and high-risk results (≥3 new RWMA) in 5% of cases. Patients with positive Dobutamine SE were more likely to be older males with traditional cardiovascular risk factors, particularly dyslipidaemia (64% vs. 59%, *P* = 0.031) and diabetes mellitus (34% vs. 29%, *P* = 0.036). They exhibited a higher burden of established disease, reflected by greater use of beta-blockers, ACE-I/ARB, anti-platelets, and nitrates, as well as higher QRISK3 scores (median 9.6 vs. 8. 1, *P* < 0.008). These findings align with established literature showing that male sex, dyslipidaemia, diabetes, and the use of cardiovascular medication predict inducible ischaemia on stress testing.^7,8^

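### The QRISK3 comparison covers the whole cohort, prior CAD included, so part of any gain for machine learning can come merely from knowing who already has the disease

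*Protocol article*

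**What the plan says.** Under QRISK3 risk estimation, the article describes the score as follows: "QRISK3 is a validated clinical risk prediction model designed to estimate the 10-year risk of cardiovascular disease (CVD) using demographic and clinical variables". The same section fixes its role: "In this study, QRISK3 is used as a benchmark model against which ML-based approaches are evaluated". Baseline performance evaluation and Statistical methods repeat that added value is judged against QRISK3. Stage 3 sets the ML score against two base models, QRISK3 and stress echo (SE) positivity. The reclassification framework then builds R0 partly from the score: "Baseline risk for each patient will be defined using conventional clinical assessment and QRISK3 derived estimates". NRI and IDI are computed from that baseline.

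On who is in the cohort, Inclusion criteria say: "The study includes consecutive patients, 18 years or older, referred for a SE for inducible ischaemia detection for suspected CAD". Exclusion criteria cover poor-quality echo descriptions, allergy, data opt-out, and patients "referred for structural SE to assess severity of valvular abnormalities or left ventricular viability only were excluded". Known CAD is not among them. Data collection lists, among the cardiovascular risk factors, "family history of CAD, diabetes mellitus, essential hypertension, dyslipidaemia, prior CAD".

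On what the models see, Stage 2 says: "Supervised machine learning models are developed using demographic characteristics, clinical risk factors, physiological measurements obtained during SE, and imaging-derived variables".

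No section restricts the QRISK3 comparison to patients without prior CAD, stratifies it by prior CAD, or adds prior CAD to the benchmark. Table 1 gives QRISK3 overall and by SE result only, and has no row for prior CAD.

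**The concern.** A comparison of two predictors isolates the value of a method only if both sides may use the same basic facts. Here one side can use prior CAD, resting wall motion and ejection fraction. The other is a score built from demographic and clinical variables, with no provision described for patients who already have the disease. If the score does not use prior CAD, a model can improve on it through that one history item, with no machine learning and no stress response involved.

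The article expects to show the incremental value of ML and to turn it into risk categories meant to influence care. A gain that partly reflects existing disease would be credited to the wrong source. It would also be concentrated in one identifiable group, so the whole-cohort figure would not describe patients without known CAD.

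**Working it through.** **Is established CAD plausibly present?** The article gives no count. Indirect signs in Table 1 are anti-platelet use in 1346/2263 = 59.5% and a resting WMSI upper quartile of 1.18 (1.18 × 17 segments = 20.06, against 17 if all segments are normal). The discussion says of SE-positive patients: "They exhibited a higher burden of established disease". These suggest some prior CAD but do not measure it.

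**How much could a prior-CAD flag add by itself?** The plan has no figure to reproduce, so this is an illustration.

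*From Table 1:* QRISK3 median 8.4%, quartiles 3.4% and 15.2%. Taking logit(QRISK3) as normal:
- mean = ln(0.084/0.916) = −2.389
- SD = [ln(0.152/0.848) − ln(0.034/0.966)] / 1.349 = (−1.719 + 3.347)/1.349 = 1.207

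*Assumed, not in the article:* prior-CAD prevalence 10–40%, odds ratio (OR) 1.5, 2 or 3, event rate 15% or 25%, coefficient b on logit(QRISK3) 0.5 or 1.0, prior CAD independent of QRISK3, no prior-CAD term in QRISK3, and NRI cut-points of 10% and 20%.

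*Model:* logit P(event) = a + b × logit(QRISK3) + ln(OR) × prior CAD, simulated in 1,000,000 patients. QRISK3 alone (recalibrated for the NRI) is compared with QRISK3 plus the flag.

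| b | Event rate | AUC gain | Categorical NRI |
|---|---|---|---|
| 0.5 | 15% | 0.004–0.058 | 0.012–0.207 |
| 0.5 | 25% | 0.004–0.059 | 0.008–0.168 |
| 1.0 | 15% | 0.002–0.028 | 0.005–0.096 |
| 1.0 | 25% | 0.002–0.028 | 0.005–0.092 |

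One mid-range case has prevalence 30%, OR 2 and event rate 15%. With b = 0.5, AUC goes from 0.657 to 0.681 and NRI is 0.079. With b = 1.0, AUC goes from 0.778 to 0.789 and NRI is 0.035. With prevalence set to 0, both gains are exactly 0.

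**Calibration.** Suppose QRISK3 were exactly calibrated in patients without CAD. Then with prevalence 10–40% and OR 2–3, the observed-to-expected ratio for the whole cohort is 1.06–1.43, while it stays at about 1.0 in patients without CAD.

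**The minimum-change rule.** The framework counts a reclassification only when risk moves by more than a threshold expected to be 3–5 percentage points. At the median, the odds are 0.084/0.916 = 0.0917. Multiplying by the odds ratio and converting back:
- OR 1.5: 0.1376/1.1376 = 12.1%, a shift of 3.7 points
- OR 2: 0.1834/1.1834 = 15.5%, a shift of 7.1 points
- OR 3: 0.2751/1.2751 = 21.6%, a shift of 13.2 points

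An odds ratio of 2 for this one item passes the filter anywhere in its range. A category change is still needed as well.

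**Do other elements of the plan remove the problem?**
- Intercept-and-slope recalibration keeps the ranking of patients (for a positive slope), so it cannot change the AUC of QRISK3. The NRI gains above are already after recalibration.
- SE positivity, the other Stage 3 base model, does not record prior CAD.
- The clinical-assessment part of R0 could carry it, but the article does not define that part as a risk estimate.

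**The case against.** Four objections carry weight.

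1. The article does not list the QRISK3 inputs and refers their extraction to a supplement that is not shown. It also does not say the score is limited to people free of cardiovascular disease. A reader might infer that QRISK3 is invalid, or too low by construction, in patients with prior CAD. The document does not support that, and the point here does not need it. It does need QRISK3 as computed to lack a prior-CAD term, which remains an assumption for the sponsor to confirm.

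2. The amount of prior CAD is unknown and the signs are weak. Referral was for suspected disease. Statin use (58%) is close to dyslipidaemia (59%), hypertension is present in 61%, ejection fraction is preserved in 95%, and resting WMSI in SE-negative patients is 1.00 (1.00–1.12). The remark on established disease is itself inferred from drug use. Even so, if nobody had prior CAD, recording it would serve little purpose.

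3. QRISK3 is not the only comparator. Stage 3 adds SE positivity, and the Stage 2 section on model development lists logistic, LASSO and Cox models on the selected features, which may include prior CAD. No comparison is ranked as primary, so calling the study's main comparison biased would go too far. But none of these models is named as the reference for reclassification.

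4. Prior CAD is not named as a model input; it belongs to a class that is, and feature selection decides what enters. A reader might conclude that any model holding the flag must beat QRISK3 on every metric. That does not follow: the model can gain this way, but better calibration in held-out data is not guaranteed.

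An unseen analysis plan might stratify by prior CAD. The article nevertheless fixes the benchmark and applies it to every patient without that qualification.

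**Conclusion.** The point holds as a should-fix. As written, the comparison with QRISK3 cannot separate the contribution of machine learning and stress data from knowledge of existing CAD. The size of that contribution in this cohort is not known. The illustrative range, about 0.002–0.06 in AUC and 0.005–0.21 in categorical NRI, runs from negligible to material and depends on the assumed prevalence, odds ratio, event rate and QRISK3 coefficient. It also takes prior CAD as independent of QRISK3. It shows the mechanism and does not estimate bias in this study. Nor does it show that all of an observed gain would come from this source. The result that depends least on those choices is that the flag contributes nothing once patients with prior CAD are left out.

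**What to change.** - Report the number and percentage with prior CAD, and with other prior cardiovascular disease, at the index SE, and add them to Table 1. State whether QRISK3 as computed uses either.
- Make the comparison with QRISK3 (AUC, calibration, NRI, IDI and the R0 categories) in patients without prior CAD or other cardiovascular disease at the index SE.
- For the whole cohort, or for the prior-CAD stratum, compare ML with a regression benchmark fitted in the development set. It should hold QRISK3 or its variables, prior CAD (where it varies) and the SE result.
- Keep the whole-cohort comparison with QRISK3 alone as a secondary result, labelled as such.

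The cost is plan wording and a stratified analysis on a variable that is already collected. The price is fewer patients and events in the QRISK3 comparison, hence wider intervals, and probably a smaller apparent gain. The article reserves the comparative performance results for the main results paper, so the change can still be specified before they are reported.

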#### Data sources and extraction

Data were obtained from institutional EHR and SE databases, including demographic information, medical history, laboratory measurements, medication records, and imaging-derived parameters. During data extraction, quality control procedures were applied to identify missing values, inconsistencies, and outliers. All data processing and cleaning were performed using Python-based data analysis tools. Extracted variables were structured into a unified tabular format suitable for statistical analysis and ML modelling.

#### Baseline performance evaluation

Baseline predictive performance will be established using QRISK3 risk estimates. Model performance will be assessed using accuracy, sensitivity, specificity, and area under the receiver operating characteristic curve (AUC, ROC). Calibration analysis and ROC curves will be used to compare predicted risk with observed outcomes. These results serve as a reference for assessing the added value of ML-based models.^13–18^

#### Data preprocessing

Prior to ML modelling, the dataset will undergo a structured preprocessing pipeline to ensure data quality and analytical robustness.

Data cleaning: Duplicate records, implausible values, and inconsistencies were identified and corrected where appropriate. Outliers were assessed using statistical and clinically informed thresholds.Missing data handling: The extent and pattern of missing data are assessed prior to analysis. Continuous variables are imputed using median, k-nearest neighbour (KNN), or multiple imputation methods, as appropriate, while categorical variables are imputed using mode-based methods. To minimize information leakage, imputation is performed using the training dataset only, with the learned imputation parameters subsequently applied to the validation dataset. No clinically implausible default values were assigned during preprocessing.Feature scaling: Continuous variables were standardized or normalized to ensure numerical stability and compatibility across ML algorithms.Categorical encoding: Categorical variables (e.g. sex, smoking status, ethnicity) were converted into numerical representations using appropriate encoding techniques.Feature engineering: Additional clinically relevant variables, including stress–response and haemodynamic indices, were be derived from existing measurements.Class imbalance handling: Outcome imbalance will be assessed and addressed using strategies such as class weighting or oversampling within the training dataset.Data partitioning: The dataset is randomly divided into development (80%), internal validation (20%) cohorts using stratified sampling to preserve event rates across all datasets. Hyperparameter optimization is restricted to the development cohort with internal validation performed exclusively within the validation dataset.

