### Stage 3: model evaluation, longitudinal risk prediction using NHS England (aka digital) data

In the final stage, the local Hospital dataset was linked with NHS England longitudinal records, which include confirmed cardiovascular events. The performance of ML score to predict clinical events will be evaluated against base models of QRISK3, and SE ischaemia positivity. The forecasting power of future cardiovascular events over 5-year and 10-year will be assessed.

This longitudinal modelling framework enables dynamic risk prediction and supports early identification of individuals at elevated risk of adverse cardiovascular outcomes. We will be inviting external sites for validation and testing the robustness and scalability of the developed predictive algorithm in all spectra of SE modalities.

Internal validation once completed external validation is performed using independent multicentre cohorts, including EVAREST and Stress Echo 2030 to assess generalisability of the model. Model discrimination will be assessed using the area under the receiver operating characteristic curve (AUC) with 95% confidence intervals (CIs). Calibration will be evaluated using calibration-in-the-large, calibration slope, observed-to-expected event ratios, calibration plots, and the Brier score. Where systematic miscalibration is identified, model recalibration using intercept and slope adjustment will be undertaken prior to assessing clinical utility by. using risk reclassification analyses, including the net reclassification improvement (NRI).

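### Class rebalancing shifts predicted probabilities upward, yet no correction is required before those probabilities are used as absolute risks in internal selection, scoring and categorisation

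*Protocol article*

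**What the plan says.** Four places in the protocol article bear on this.

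- **Data preprocessing** (class imbalance handling): "Outcome imbalance will be assessed and addressed using strategies such as class weighting or oversampling within the training dataset". No target ratio is given, and no correction of the resulting probabilities is attached.
- **Stage 2**: "Model selection is based on discrimination, calibration, robustness across validation folds, and clinical interpretability". Calibration is a criterion for choosing a model, but no corrective step is named.
- **Stage 3**: "Calibration will be evaluated using calibration-in-the-large, calibration slope, observed-to-expected event ratios, calibration plots, and the Brier score". It continues: "Where systematic miscalibration is identified, model recalibration using intercept and slope adjustment will be undertaken prior to assessing clinical utility", and names risk reclassification, including NRI, as the way clinical utility is assessed. Both sentences stand in the paragraph that opens with external validation in independent multicentre cohorts.
- **FINESSE AI–based risk reclassification framework**: "continuous risk estimates will be mapped to predefined categories using a threshold-based classification function". A move between categories counts only if "the absolute change in predicted risk exceeds a predefined threshold, anticipated to be in the range of 3–5 percentage points". The comparator is a baseline risk built on clinical assessment and QRISK3. The category thresholds are to be checked against observed event rates in the cohort. The framework is then judged by AUC, calibration plots, Brier score, NRI and IDI.

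**The concern.** A classifier trained on rebalanced data estimates risk for an artificial population with more events than the real one. Ranking, and so AUC, is little affected, but the level of the predicted probability moves up. QRISK3 stays on its own scale of 10-year risk. If the two are compared without correction, part of the difference comes from the training method and not from the stress echo information.

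Several internal results depend on the level of the predicted probability:

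- The Brier score of a rebalanced model is made worse.
- IDI compares mean predicted risk in patients with and without events, so it changes when the probability scale is stretched.
- Model selection on calibration would penalise an algorithm for how it was trained and not for its merit.
- Category assignment and the 3–5 point limit act directly on the shifted number.

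If the first correction happens in the external cohorts, it also mixes a shift created in training with genuine differences between populations, which external validation is meant to measure.

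**Working it through.** **Inputs.** The article states no event rate for any endpoint or horizon and no rebalancing ratio, so there is no figure of its own to reproduce. The event rates p below are assumptions. The 3–5 point limit is from the reclassification framework section. The median QRISK3 of 8.4% is from Table 1 and serves only as an example of a true risk. The 80%/20% split is from Data preprocessing; applied to 2263 patients it gives about 1810 and 453.

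**Formula.** Balancing events and non-events 1:1 multiplies the odds by k = (1−p)/p. For a true risk r:

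shown risk = k·r/(1−r) ÷ [1 + k·r/(1−r)]

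Example: p = 10% gives k = 0.90/0.10 = 9. For r = 5%, the odds are 0.0526 × 9 = 0.474, and 0.474/1.474 = 32.1%.

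| Assumed event rate p | Odds multiplied by | Patient at average risk (r = p) shown | Ratio to truth | True 5% shown as | True 8.4% shown as |
|---|---|---|---|---|---|
| 5% | 19 | 50% | 10 | 50.0% | 63.5% |
| 10% | 9 | 50% | 5 | 32.1% | 45.2% |
| 20% | 4 | 50% | 2.5 | 17.4% | 26.8% |
| 30% | 2.33 | 50% | 1.7 | 10.9% | 17.6% |
| 40% | 1.5 | 50% | 1.25 | 7.3% | 12.1% |

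**Against the 3–5 point limit.** The patient at average risk moves by 45, 40, 30, 20 and 10 points, which is above the limit throughout. At p = 40% the low-risk examples move much less: 12.1 − 8.4 = 3.7 points, and 7.3 − 5 = 2.3 points.

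**Partial balancing.** If events are raised only to one third of the training data, the average patient is shown 33.3%. That is 6.7, 3.3, 1.7 and 1.1 times the truth at event rates of 5%, 10%, 20% and 30%.

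**Simulation check.** The set-up was a logistic model with five predictors, 1810 development patients, balanced class weights, 40 replicates and a test set of 20,000. Intercept and slope were recalibrated on 453 further patients. The 16.4% rate is 371/2263, the share with positive stress echo, borrowed only as one illustrative event rate.

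| Event rate | Mean predicted/observed, weighted | Share moved up by more than 5 points against the unweighted model | Predicted/observed after recalibration | Brier: weighted / recalibrated / unweighted |
|---|---|---|---|---|
| 5% | 8.3 | 99.1% | 1.01 | 0.206 / 0.046 / 0.046 |
| 10% | 4.3 | 99.3% | 1.03 | 0.207 / 0.083 / 0.083 |
| 16.4% | 2.7 | 99.3% | 0.97 | 0.207 / 0.122 / 0.122 |
| 30% | 1.6 | 98.6% | 1.01 | 0.210 / 0.181 / 0.180 |

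Two things follow. Recalibration repairs the shift almost completely when it is done on clean data. Rebalancing followed by repair only returns the model to where it would have been without rebalancing.

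**Does the plan guarantee the repair in time?** Data preprocessing, Stage 2 and the reclassification framework section name checks but no correction. Stage 3 names a correction, conditional on a finding of miscalibration, ahead of NRI, and without saying which data fit it. The 453 recalibration patients in the simulation were separate from both development and test data. The 80%/20% split sets no such group aside, and using the 20% for recalibration would end its role as an untouched internal validation set.

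**The case against.** The strongest reply is that the plan already contains the cure. Stage 3 places intercept and slope recalibration ahead of the reclassification analysis, and the calibration measures listed there would hardly miss a large shift. Stage 2 selects on calibration, and the category thresholds are checked against observed event rates. All of this stands, and it rules out several stronger readings that a reader might infer.

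- **That NRI would be computed on inflated risks.** Not supported. Stage 3 puts recalibration before NRI, so NRI is exposed only if that step is not triggered or is not applied to the internal data.
- **That risks are inflated several-fold.** Not supported as a fact. Imbalance is first to be assessed, the techniques are examples, and no ratio or event rate is stated. The Outcomes section reaches to 10–20 years with all-cause death and broad composites, so high event rates are possible. At 30–40% the average patient's inflation is about 1.25–1.7-fold.
- **That most patients would change category.** Not shown. A change of category is needed as well as a shift above the limit, and the cut-points are not given. Discordant cases go to clinical review and are not reassigned automatically.
- **That every model is affected.** Not supported. The Cox and random survival forest models use event times, and the formula does not carry over to them.
- **That recalibration is confined to the external cohorts.** This rests on sentence order. Stage 3 opens with the local linked cohort, and the text does not limit the step to external data.

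It can also be said that a condensed article may leave the fitting data to a fuller document. That is fair for the detail. But the article does affirmatively name a training method that works against its own use of absolute risk, and the checks it lists detect a shift without removing it.

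**Conclusion.** The point holds in a limited form and should be addressed. Class weighting or oversampling shifts the probabilities of the classification models upward, and the framework uses those probabilities as absolute risks. Uncorrected, 1:1 balancing would show the average patient 50%, between 10 times (5% events) and 1.25 times (40% events) the true risk, and would create artefactual upward shifts relative to QRISK3.

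The planned recalibration can remove this, but it is conditional, stands in the external-validation paragraph and names no fitting data. Internal model selection, Brier score, IDI and category assignment may therefore rest on shifted risks.

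The size depends on assumed event rates, on full 1:1 balancing and, for the simulation, on a simple logistic model. The direction is the same for the other classifiers, but the amount need not follow the formula exactly.

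**What to change.** Change the class-imbalance sentence in Data preprocessing so that classification models whose output is used as a risk are trained at the natural event rate.

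If rebalancing is kept, add three requirements:

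1. Intercept and slope are always re-estimated on unbalanced, out-of-fold predictions from the development cohort, not only when miscalibration is noticed.
2. This happens before any model selection, category assignment, or internal or external evaluation, and without using the 20% validation set.
3. External calibration is reported for the model as delivered, before any recalibration in the external cohorts.

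The first option is a one-sentence change and less work. The second adds one fitting step that uses predictions the cross-validation already produces. The downside of dropping rebalancing is that sensitivity at a default 50% cut-off will look lower. The framework classifies by prespecified risk thresholds, so sensitivity is better reported at those.
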